### Study intervention and procedures

The patients will be scheduled for clinical assessment in the PITAC outpatient clinic including bedside ultrasound of the pleural cavity and information about the study. Included patients will be scheduled for a maximum of three PITAC procedures and minimum of two PITAC procedures at four-week intervals (Figure 1).

**Figure 1: j_pp-2024-0014_fig_001:**
[figure not shown]
Study flow chart ^a^if visible PLM; ^b^if less than 150 mL of MPE present. AEs: adverse events; FEV1: forced expired volume in the first second; MDT: multidisciplinary tumour; MPE: malignant pleural effusion; PITAC: pressurized intrathoracic aerosol chemotherapy; PLF: pleural lavage fluid; PLM: pleural metastasis; SAT: saturation; TRGS: thoracic regression grading score; VAS: visual analogue score.

Patients may have a pleurocentesis up to 14 days before the planned PITAC directed treatment. In case the patients require drainage of MPE between PITACs, this is possible as an outpatient procedure and registered to ensure that the accumulative amount of MPE from the first PITAC directed treatment can be calculated. Patients may receive treatment with systemic chemotherapy or immunotherapy up to 14 days before PITAC treatment, and antihormonal, tyrosine kinase inhibitor (TKI) and/or steroid treatment may be given continuously. The wash out period from PITAC to systemic chemotherapy or immunotherapy is one week.

### Preoperative procedure

Baseline blood samples are taken two days before each PITAC. Prophylactic low molecular weight heparin is given before and after the procedure. Oxygen saturation (SAT), forced expired volume in the first second (FEV1), and visual analogue scale (VAS) pain and breathlessness will be measured before each PITAC.

### PITAC

The procedure will be performed in an operating room (OR) with a modern direct flow ventilation system that complies with ISO norm class 5. The chemotherapy is evacuated through a closed air waste system at the end of the procedure. The operating personnel will wear protective barrier garments, double layered gloves and glasses throughout the entire procedure.

Prior to general anaesthesia a bedside ultrasound is performed in the OR to ensure the presence of MPE. General anaesthesia and prophylactic antibiotics are administered and the patient is intubated in the supine position and flipped into the prone position. In the prone position ultrasonography is repeated to ensure optimal access to the pleural cavity, and the first entry point is marked with a pen before surgical dressing is applied. Under video-assisted thoracoscopy two trocars (5 and 12 mm) are placed and exclusion of the ipsilateral lung is confirmed when relevant. MPE is removed (and submitted for cytology) and measured and the extent of visible PLM is assessed macroscopically using the PLM-score (Figure 2). If no or only small amounts of MPE are present, pleural lavage is performed and PLF is submitted for cytology. The PLM-score is a modification of the known PCI-score. The parietal pleura is divided into four quadrants and assessed on a scale from 0-3 depending on the size of visible tumour lesions (Figure 2). Quadrant biopsies are taken from visible PLM on the parietal pleura for histological assessment.

**Figure 2: j_pp-2024-0014_fig_002:**
[figure not shown]
Macroscopic evaluation of visible pleural metastasis (PLM) (PLM-score).

The CE-certified nebulizer is inserted pointing away from lung tissue. A safety checklist is followed to ensure maximum safety for both patients and personnel.

PITAC is performed at an intrapleural pressure of 12 mmHg using normothermic carbon dioxide (CO_2_). The injector is controlled from outside the OR and the settings will be a maximum of 300 pound-force per square inch (Psi) with a flow-rate of 0.5–1.8 mL/s as defined for the used nebulizer. Diffusion time is 30 min. The injector and patient observation monitors are visible through a window.

The chemotherapy filled air in the pleural cavity is removed through a closed air waste system. Sufficient re-ventilation of the ipsilateral lung is ensured when relevant/possible. The two trocar access points are closed with suture in both the fascia and skin. Chest tubes are not used routinely. Local anaesthetics are applied at the trocar sites.

### Histology

Quadrant parietal pleural biopsies will be collected, if possible. The biopsies will be fixed in formalin and embedded in paraffin followed by step-section at three levels, and stained with haematoxylin and eosin (H&E), followed by a section immunostained for epithelial cell adhesion molecule (Ep-CAM (or Hector Battifora and MEsothelioma 1, HBME1, in case of malignant mesothelioma)), and a final series of three step sections stained with H&E [24, 25]. Additional immunostains will be used at the discretion of the pathologist. Histological response to treatment will be assessed in each biopsy according to the proposed TRGS, a modification of the Peritoneal Regression Grading Score (PRGS) [23, 26, 27]. TRGS-1 equals complete histological response, and is defined as the absence of residual cancer and harbours only regressive histological features. TRGS-2 is defined as a biopsy where regressive changes are predominant over cancer cells (major response). TRGS-3 is a biopsy where cancer cells are predominant but regressive changes are present (minor response), and TRGS-4 is a biopsy with cancer but without histological features of regression (no response).

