#### Primary and secondary objectives

This is a Phase-I study investigating safety and feasibility of repeated PITAC (minimum of two procedures) in 20 patients. PITAC is considered feasible and safe if four patients or less have severe surgical complications defined as Clavien-Dindo ≥ 3b or life-threatening adverse events (AE) defined as Common Terminology Criteria for Adverse Events v. 6.0 (CTCAE) ≥ 4 within 30 days after the procedure. All medical AEs and surgical complications will be recorded, but only those who are probably or certainly/definitely related to the PITAC directed treatment will provide grounds for assessing the feasibility and safety.

Secondary objectives include (1) macroscopic evaluation of PLM before and after PITAC and evaluation of histological response using a proposed Thoracic Regression Grading Score (TRGS) in biopsies from visible PLM and MPE [23], (2) evaluation of response by pleural lavage fluid (PLF) or MPE cytology, (3) assessment of personnel safety (environmental and biological), and (4) evaluation of the quality of life with EORTC-QLQ-C30 at baseline, day 30 and three months after the last PITAC directed treatment.

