### Study design

This is a non-randomized, non-blinded, prospective, single-center phase-I study designed to treat patients with MPE from any primary tumour with PITAC.

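### TRGS reading is not exempted from the non-blinded design, and its line between major and minor response (grade 2 against 3) is an unquantified judgement; masked scoring would be a cheap improvement

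*Protocol article*

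**What the plan says.** All references are to the protocol article.

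- **Histology:** "Histological response to treatment will be assessed in each biopsy according to the proposed TRGS". Grade 1 requires "the absence of residual cancer and harbours only regressive histological features". For the next level, "TRGS-2 is defined as a biopsy where regressive changes are predominant over cancer cells", labelled a major response. Grade 3, labelled minor, is the reverse balance: mostly cancer, with some regression. Grade 4 is cancer with no sign of regression. No percentage or area rule defines predominance. The score is called proposed and is adapted from the peritoneal score.
- **Study design:** "This is a non-randomized, non-blinded, prospective, single-center phase-I study". No assessor is exempted.
- **Primary and secondary objectives:** histological response by TRGS is part of secondary objective (1). The primary criterion counts severe complications and adverse events.
- **Study intervention and procedures:** each patient is scheduled for two or three PITACs, four weeks apart.

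**The concern.** Patients and surgeons cannot be masked to which PITAC is being given, but a reader of stained slides can be. The Histology section is detailed on fixation, step sections and immunostaining. It says nothing on the conditions of reading, and the only statement on blinding in the article is the general one.

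At stake is one of the few local-effect results that the study offers. The abstract names local response among the matters on which prospective data are lacking, and it expects the results to shape the next steps for PITAC. If borderline slides from later procedures are graded 2 where a masked reader would give 3, part of the apparent response comes from the reading and not from the tissue.

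**Working it through.** The article gives no figure for TRGS to reproduce, so the check sets the sections side by side.

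**1. Which boundaries need the predominance call?**

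| Boundary | What decides it (Histology) | Predominance call? |
|---|---|---|
| 1 against 2 | residual cancer absent or present | no |
| 2 against 3 | which component predominates | yes, no cut-off |
| 3 against 4 | regressive features present or absent | no, though judgement is still needed |

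Only one of the three boundaries rests on predominance. It is the one that separates major from minor response.

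**2. What is the contrast?** The abstract calls the study controlled, but the article describes no comparator, and Study design says non-randomized. Biopsies are taken at PITAC procedures; the three-month visit lists CT, ultrasound and lung measurements, not biopsy. A change in grade can therefore be seen only from PITAC 1 to PITAC 2 or 3. For the slide reader, the procedure number is the treatment status.

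**3. Is masking excluded, provided or left open?** Study design labels the whole study non-blinded. Histology neither makes an exception nor states that the reader knows the procedure number. The plan as written leaves the path for expectation bias open; it does not show that the path is used.

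**4. Can the size be derived?** With one response status per patient (an assumption, since TRGS is graded per biopsy and the article gives no rule for combining biopsies):

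expected spurious major responses = (patients with paired biopsies) × (share near the 2/3 line) × (probability that knowing the procedure number moves the grade)

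- First term: Sample size targets 20 completers, so at most 20 pairs among them. The number may be well below that, because biopsies depend on visible pleural metastasis and on feasibility, while eligibility requires effusion only.
- Second and third terms: not given. The article has no reader-agreement figure and no expected grade distribution.

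The product cannot be computed. What can be shown is the weight of one reclassified patient: 1/20 = 5 percentage points with 20 pairs, or 1/10 = 10 points if only 10 pairs were available. This is the granularity of the result and not an estimate of bias.

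**5. What depends on TRGS?** The safety criterion (Primary and secondary objectives) and the stopping rule (Interim analysis) use only complications and adverse events. Neither the target of 20 nor any decision in the article waits for a TRGS grade.

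**The case against.** The strongest reply is that this is a condensed article. Reading order, slide coding and the reader's access to clinical data are commonly left to the full protocol, which is not shown. On that view, non-blinded is a one-line label for a study without a comparator and says nothing about the pathologist. Part of this stands: unmasked reading is an inference, and the full protocol may already provide for masking. But the article does not merely stay silent on blinding. It states the design as non-blinded without exception, beside a graded outcome with an unquantified boundary.

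Other points on that side also stand:

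- The step sections and the immunostain support the call on residual cancer, and the score builds on an existing one.
- The expectations that the article states concern safety, feasibility and effusion volume, not TRGS.
- Systemic therapy is allowed between PITACs, subject to wash-out, so even masked grades would not attribute regression to PITAC alone.

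A reader might go further and infer that the slides are known to be read unmasked, that the whole score turns on predominance, or that a particular number of false responses will follow. The document supports none of these (steps 1, 3 and 4). Nor would a reading bias be beyond recovery: the biopsies are fixed and embedded in paraffin, so a masked re-reading could check an apparent shift.

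**Conclusion.** The point holds as a low-cost improvement of minor severity. The article declares the study non-blinded without exempting histology, and the line between major and minor response has no numeric definition. In a comparison of earlier with later procedures, a reader who knows the procedure number could shift borderline grades toward response.

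This is conditional on the pathologist having that knowledge, which the article does not state. The size of any bias is unknown and cannot be derived. The effect is confined to the histological part of secondary objective (1). It would be wrong to infer that the safety conclusion is weakened, because no safety rule uses TRGS.

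**What to change.** Add a statement to Histology along these lines: for the study endpoint, TRGS is scored by the existing pathologist from coded slides in random order, masked to PITAC number and sampling date, in one batch after the patient's last PITAC and separately from the routine diagnostic report. Slide labels should carry no laboratory number or date from which the order could be read. If the full protocol already provides this, one sentence in the article settles the point.

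**Cost:** no extra reader, biopsy or patient procedure, and routine reporting is unchanged. If each quadrant yields one biopsy (an assumption), 20 completers with two or three procedures and four quadrants give at most 20 × 2 × 4 = 160 to 20 × 3 × 4 = 240 biopsies to code and score. Fewer are likely, since only visible disease is sampled.

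**Downside:** TRGS results come later and slides are handled again. Masking is incomplete if the same pathologist issued the routine report and recognises a specimen.

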### Cytology

A maximum of 250 mL MPE or PLF pr. PITAC procedure will be collected and analysed. Pleural lavage is performed in cases with no or less than 200 mL of MPE present in the pleural space. The fluid will be centrifuged, and smears of the sediment analysed by conventional cytology (Papanicolaou and May-Giemsa Grünwald staining). Leftovers of the sediment will be embedded in paraffin wax of which one section will be stained with H&E. If necessary, further sections will as part of the standard routine be cut for immunocytochemical analyses for markers such as calretinin, thyroid transcription factor 1 (TTF1), carcinoembryonic antigen (CEA), cytokeratin (CK) 7, CK20, synaptophysin, cluster of differentiation (CD) 56 or P40. The cytological specimens will be categorized as one of the following: Malignant cells, cells suspicious of malignancy, atypical cells, no malignant cells, or ”inconclusive” (for technical reasons).

### Chemotherapy

Depending on the primary tumour and previous/bidirectional systemic chemotherapy, the following regimes will be applied: Patients with MPE from non-colorectal or -appendix cancer will be treated with cisplatin (10.5 mg/m^2^ body surface in 150 mL saline) and doxorubicin (2.1 mg/m^2^ body surface in 50 mL saline). Patients with MPE from colorectal or appendiceal cancer will receive oxaliplatin (92 mg/m^2^ body surface in 150 mL dextrose).

Cisplatin, oxaliplatin and doxorubicin are standard, commercially available cytostatic drugs in oncologic treatment with alkylating and topoisomerase inhibitor effect, respectively. The most common side effects of administering Cisplatin and oxaliplatin intravenously are: Fever, nausea, diarrhoea, kidney failure, pancytopenia and ototoxicity. With regard to doxorubicin, it is furthermore: Debilitation, shivers, infections, skin eruptions, electrocardiogram changes, thrombophlebitis and deep venous thrombosis. Based on the literature and experience gained from more than 1000 PIPAC procedures at OPC, PIPAC (i.e. local treatment) with cisplatin, oxaliplatin and doxorubicin is well tolerated with only a minimal of nausea, vomiting and transient abdominal pain. The experience with PITAC directed therapy is limited, but the above mentioned systemic adverse events from cisplatin, oxaliplatin and doxorubicin are not expected with PITAC directed treatment. The use of cisplatin 10.5 mg/m^2^, oxaliplatin 92 mg/m^2^ and doxorubicin 2.1 mg/m^2^ are based on dose finding studies, stating that the above-mentioned dosages are safe for intraperitoneal use [28, 29].

### Postoperative procedure

The patient is monitored for a minimum of one day. A chest X-ray is performed if the patient shows signs of respiratory distress to consider the indication for a chest tube. SAT, FEV1, and reactions/complications will be registered before discharge of the patient.

Thirty days after each PITAC directed therapy the patient will attend an outpatient appointment for bedside ultrasound and registration of postoperative reactions/complications. The 30 day follow-up must be collected prior to the next PITAC directed treatment.

The last follow-up including a CT scheduled three months after the last PITAC. Furthermore, patients will be evaluated in the outpatient clinic including bedside ultrasound, SAT and FEV1.

### Occupational health safety aspects

Summarized, there are three barriers between personnel and the chemotherapy: The closed intrathoracic cavity, the modern OR ventilation with a direct air-flow system, and the OR walls. Possible air-leakage is controlled by allowing a maximum of CO_2_ flow of 0.1–0.2 L/min corresponding to the intraperitoneal body resorption of CO_2_. The intrapleural air saturated with chemotherapy is evacuated through a series of filters into a closed ventilation system. Special chemotherapy waste bins are available for all single-use equipment and the trocar sites, removal and disposal of dressings and syringes are performed by the surgeon alone.

From previous PIPAC knowledge, is has been demonstrated that the procedure is safe in terms of the personnel safety and fulfils the European Community working space law. It is theorized that these data can be directly transferred to the PITAC procedure [12, 14]. Danish Technological Institute will analyse the toxicological workspace for traces of platinum to validate the occupational health safety during PITAC.

In the present study, blood samples from the surgeons will be analysed for traces of platinum immediately after the first procedure and again after the 10th procedure. The surgeons also perform weekly PIPAC procedures. Previous tests for platinum in the surgeońs blood after PIPAC were negative, why we expect only negative results [12].

### Study design

This is a non-randomized, non-blinded, prospective, single-center phase-I study designed to treat patients with MPE from any primary tumour with PITAC.

### Sample size

There are no data to support the estimated number of patients needed for this phase-I study. The non-access rate, based on previous experience, is estimated to 20 %. This study will include consecutive MPE patients until 20 patients have completed at least two PITAC procedures. Interim analyses will be performed in order to monitor patient safety.

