Patients will be excluded from the study if (1) requested by the patient, (2) access to the pleural cavity is not possible due to adhesions or other technical aspects, and/or (3) decline in general health resulting in Eastern Cooperative Oncology Group (ECOG) performance status higher than 2. Following events are considered sufficient reasons for discontinuing a subject from the study (1) withdrawal of consent, (2) death, (3) loss to follow up and/or (4) severe AE or surgical complications. The following information will be recorded for patients who have been excluded from the study: Survival, amount and frequency of MPE drainages and illness specific variables (e.g. CT-scan results).

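### The limit of four patients has no stated safety set: the only 20 patients defined are those who completed two PITACs, so events after a first PITAC and failed access can fall outside the verdict

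*Protocol article*

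**What the plan says.** Under Primary and secondary objectives, the protocol article describes a study of "safety and feasibility of repeated PITAC (minimum of two procedures) in 20 patients". The decision rule follows: "PITAC is considered feasible and safe if four patients or less have severe surgical complications" or adverse events of CTCAE grade 4 or above within 30 days. Only events judged probably or definitely related count. The rule names no analysis set and no denominator.

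Sample size says who the 20 are: "This study will include consecutive MPE patients until 20 patients have completed at least two PITAC procedures". It estimates non-access at 20% and gives no power or precision calculation.

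Recruitment process gives two groups who leave:

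- **Excluded:** at the patient's request, because "access to the pleural cavity is not possible due to adhesions or other technical aspects", or for "decline in general health resulting in Eastern Cooperative Oncology Group (ECOG) performance status higher than 2".
- **Discontinued:** sufficient reasons are withdrawal of consent, death, loss to follow-up and "4) severe AE or surgical complications".

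For excluded patients the data to be recorded are "Survival, amount and frequency of MPE drainages and illness specific variables". Clavien-Dindo and CTCAE events are not on that list.

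Two other places bear on the point. Postoperative procedure registers complications before discharge and 30 days after each PITAC. Interim analysis sets a safety look after every 10 procedures and ends the study once four or more procedures have led to a qualifying event.

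**The concern.** The only group of 20 in the plan is selected on something that happens after treatment starts. A patient who has a severe event after the first PITAC and is discontinued cannot become one of the 20, and another patient is recruited. The same holds for a patient whose pleural cavity cannot be entered or who declines after one procedure.

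The rule can be read in two ways, and neither works as written:

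- **Completers only.** First-procedure events in patients who then leave do not count towards the four, and non-access does not enter the feasibility verdict.
- **All treated or attempted.** The denominator is open-ended, and a limit of four no longer means four in 20.

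Safety is the primary purpose of this study. The first reading can only move the result towards safe, and the second leaves the meaning of the limit to chance.

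**Working it through.** **Inputs from the protocol article:** 20 completers of at least two PITACs and 20% non-access (Sample size); a safe verdict at four patients or fewer (Primary and secondary objectives); looks every 10 procedures with a stop at four or more qualifying procedures (Interim analysis). The plan gives no operating characteristics to reproduce.

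**Assumptions:** the true risk is not known, as Interim analysis itself says, so the risk *q* of a qualifying event per procedure is varied. It is the same at both procedures, each patient has two, and an event at the first leads to discontinuation and replacement.

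**Step 1, enrolment.** With 20% of patients lost to non-access and nobody lost for another reason, 20 / (1 − 0.20) = 25 patients are needed. Four of 25 is 16%, against 20% for four of 20.

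**Step 2, completers only.** The number of completers with an event is S ~ Bin(20, *q*), so P(safe) = P(S ≤ 4).

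**Step 3, all treated.** Let F be the number of first-procedure events before the 20th completer. Then P(F = k) = C(19 + k, k) *q*^k (1 − *q*)^20, with mean 20*q*/(1 − *q*), and P(safe) = P(F + S ≤ 4).

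| Risk per procedure | P(safe), completers | P(safe), all treated | Mean first-procedure events left out |
|---|---|---|---|
| 5% | 0.997 | 0.94 | 20 × 0.05 / 0.95 = 1.1 |
| 10% | 0.96 | 0.59 | 20 × 0.10 / 0.90 = 2.2 |
| 15% | 0.83 | 0.22 | 20 × 0.15 / 0.85 = 3.5 |
| 20% | 0.63 | 0.06 | 20 × 0.20 / 0.80 = 5.0 |

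Simulation of the recruitment rule agrees with these values. If the first procedure is riskier (30%, then 10%), the pair is 0.96 vs 0.04.

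**Step 4, the reported rate.** A patient who starts has risk 1 − (1 − *q*)², while completers show *q*. At 10% this is 19% against 10%; at 20% it is 36% against 20%.

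**Step 5, the interim rule.** If every procedure is counted, cumulatively, simulation gives:

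| Risk per procedure | Trial stopped | Completer-only safe verdict with no stop |
|---|---|---|
| 5% | 14% | 0.86 |
| 10% | 58% | 0.42 |
| 15% | 87% | 0.13 |
| 20% | 97% | 0.03 |
| 30%, then 10% | 98% | 0.02 |

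A trial that passes its last look has had at most three qualifying procedures up to then. The two readings will therefore seldom give opposite verdicts in a trial that runs to the end. The gap in the reported rate (step 4) is not removed: F averages 1/(1 − *q*) times S before any stop, so about one event is left out for each one counted.

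**The case against.** The best reply is that the article never restricts the count to completers. Sample size gives a rule for when recruitment ends, not an analysis set. The objectives section says that all adverse events and complications are recorded and filters them only by relatedness. The abstract defines the primary outcome without a completion condition, and complications are registered 30 days after each PITAC. All of this stands. A reader might infer that harmed patients are dropped from the primary result; the documents do not say so. What they leave open is whether those patients' events count, because recording an event does not place it inside the limit of four.

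A reader might also infer that the primary endpoint goes unrecorded in patients who leave after a severe event. That goes too far. The short data list refers to excluded patients, whereas severe events appear among reasons for discontinuation. The list is still narrower than the endpoint and should be reconciled with the general recording rule.

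Three further points limit the size. A severe event is a sufficient reason to discontinue, not an automatic one, so full discontinuation is the upper case. Patients harmed at a second or third PITAC are completers and do count. Failed access is not itself harm; its omission bears on feasibility.

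The interim rule is the strongest mitigation. If it covers every procedure, the high chances of a false safe verdict at high risk largely disappear. It is, however, a stopping rule with its own unit, procedures rather than patients, and does not define the primary result.

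Finally, a condensed article may leave analysis populations to a fuller document. Here, though, the article itself states the limit, the 20 and the leaving rules, and these do not fit together.

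**Conclusion.** The point holds as a defect in how the primary rule is fixed. The verdict limit sits beside 20 patients defined by completing two PITACs, others are in effect replaced, and no denominator is given. Events after a first PITAC, and failed access, can therefore fall outside the safety and feasibility verdict.

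Without an interim stop the effect is modest at 5% per procedure and large from 10% upwards. These figures rest on assumed equal risks and on discontinuation after every first-procedure event; fewer discontinuations would shrink the gap. With an interim rule that counts every procedure, the chance of a completer-only safe verdict falls to 0.42 at 10% and 0.03 at 20%. It would be wrong to infer that a dangerous treatment would probably be declared safe. What remains in a trial that is not stopped is a reported event rate of roughly half the risk that a starting patient faces, and a feasibility result without the non-access patients.

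**What to change.** Change the protocol wording as follows:

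1. Define the primary safety set as every patient in whom a PITAC is attempted, including non-access, one-procedure and later excluded or discontinued patients. State the point from which an attempt counts, for example anaesthesia or first trocar.
2. Count a patient once if at least one qualifying event occurs between the first attempt and 30 days after the last.
3. State the verdict limit as a proportion of that set. Recruitment may still run until 20 patients have completed two procedures.
4. In Recruitment process, state that 30-day Clavien-Dindo and CTCAE events are kept for excluded and discontinued patients alike.
5. Report non-access separately, as a feasibility result, and show completers as a secondary table.
6. State that the interim count covers every procedure, completer or not.

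The cost is a few sentences and continued 30-day event recording in the few patients who leave early. The downside is a less favourable headline rate.
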